### Design

2.1

The following is a protocol for a prospective randomized controlled clinical trial. The trial has been registered with the Chinese Clinical Trial Registry (no ChiCTR1900028332, registered December 29, 2019). After obtaining written informed consent, a 1-week run-in period will be implemented, after which 120 eligible participants will be randomly assigned to a trial group or a control group in a 1:1 ratio. The 2 groups will then undergo treatment for 24 weeks with follow-up after 12 weeks. The study procedure is shown in Figure 1. The trial aims to investigate the additional benefits and safety of TNHCG compared to conventional drug treatment for COPD. It will adhere to the Standard Protocol Items: Recommendations for Interventional Trials (SPIRIT) 2013 statement. The schedule of enrollments, interventions, and assessments is shown in Figure 2. The SPIRIT 2013 checklist is presented as Additional File 1.

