### Sample size

2.4

Sample size calculations are based on the primary outcome (improvement in the 6-MWT). Referring to previous research by Chen et al,^[17]^ compared to the conventional treatment group, the 6-minute walking distance (6MWD) of the COPD TaiChi PR group improved by an average of 52 m (variance 77.5, correlation coefficient 0.7–0.8, power 0.90). Power analysis revealed that 96 participants, 48 in each group are required to attain a significance level of 2.5%. To avoid the decrease in sample size caused by follow-up drop-outs, the total sample size required, calculated with a 20% drop-out rate, is 120 participants with 60 participants per group.

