### Eligibility criteria

2.7

Inclusion criteria:

1.Patients aged 40 to 75 must meet the diagnostic criteria of COPD according to the GOLD guidelines; no gender and grade limitations.2.Patients with acute exacerbation periods must first be relieved before they can participate in the trial, while patients with stable COPD meet the inclusion criteria.3.Patients have no heart, liver, kidney, or mental system issues.4.Patients provide written informed consent.

Exclusion criteria:

1.Participants with other chronic respiratory diseases.2.Participants with severe comorbidities, such as tumors, symptomatic cardiovascular diseases, myocardial infarction, and neuromuscular diseases.3.Participants who are pregnant or lactating.4.Participants with AIDS, mental illnesses, and cognitive dysfunction.5.Participants who are currently practicing traditional Qigong exercises such as Baduanjin and TaiChi or are participating in other clinical trials associated with COPD.

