##### 6-Minute Walking Test

3.3.1.1

The primary outcome is the change in 6-MWD from baseline to the end of the treatment period (week 24). The purpose of this test is to measure the maximum distance that the participants can walk as fast as possible within 6 minutes on a flat surface. The 6-MWT is one of the most widely used tests to assess exercise tolerance in COPD.^[17]^ Participants will be given 400 μg salbutamol aerosol 20 min before the tests for safety.

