### Statistical analysis

3.8

All analyses will be conducted according to the intention to treat principle. Missing values will be replaced by the last observation carried forward method. Two similar participants with complete data will be double-checked to make sure that data are correct before analysis.

The data will be analyzed using the Statistical Package for the Social Sciences version 23.0 (SPSS 23.0, Chicago, IL). The analytical methods will be selected according to the distribution characteristics of the data: measurement data will be analyzed using group *t* tests or nonparametric tests, while count data will be analyzed using a Chi-square test or the Fisher exact probability method. Grade data will be analyzed using nonparametric tests. Compared with baseline values, measurement data will be assessed using paired *t* tests or nonparametric tests, and count data will be examined using a nonparametric test. All statistical tests will be bilateral tests and *P*-values <.05 will be considered statistically significant.

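### Section 3.8 ties no between-group test to the primary change in 6MWD and lists within-group paired tests at P<.05 without marking them as descriptive

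*Protocol article*

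**What the plan says.** Section 3.3.1.1 (6-Minute Walking Test) defines the endpoint: "The primary outcome is the change in 6-MWD from baseline to the end of the treatment period (week 24"). Section 2.1 (Design) puts the question between groups: "The trial aims to investigate the additional benefits and safety of TNHCG compared to conventional drug treatment for COPD".

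Section 3.8 (Statistical analysis) gives two analyses for continuous data. The first compares the groups: "measurement data will be analyzed using group *t* tests or nonparametric tests". The second works within a group: "Compared with baseline values, measurement data will be assessed using paired *t* tests or nonparametric tests". One decision rule covers both: "All statistical tests will be bilateral tests and *P*-values <.05 will be considered statistically significant".

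The section does not say whether the group t test is applied to the change or to the week-24 value. It does not name the test that decides the primary outcome, and it does not give the paired tests a lesser role.

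**The concern.** The endpoint is a change from baseline, and the only sentence in 3.8 that mentions baseline prescribes a within-group test. That test asks whether 6MWD moved in one arm. The trial asks whether it moved more with TNHCG than without.

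The two answers diverge whenever both arms shift together, and the article makes a shared shift plausible. Both arms receive standard drugs and the same COPD education (section 3.1). Recently unstable patients can also enter: "Patients with acute exacerbation periods must first be relieved before they can participate in the trial" (section 2.7), and the run-in is one week (section 2.1).

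As written, a P-value below .05 for change from baseline in the TNHCG arm has the same standing as the between-group result. It could be presented as an efficacy finding when the arms do not differ.

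**Working it through.** **1. What the sample size was built for.** Section 2.4 (Sample size) states that 6MWD "improved by an average of 52 m (variance 77.5, correlation coefficient 0.7–0.8, power 0.90") relative to conventional treatment, and that "96 participants, 48 in each group are required to attain a significance level of 2.5"%.

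The two-sample formula is n per arm = 2(z₁₋α/₂ + z₁₋β)² SD² / Δ². With Δ = 52, SD = 77.5, two-sided α = .05 and power .90:

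2 × (1.960 + 1.282)² × 77.5² / 52² = 46.7, so 47 per arm.

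The noncentral-t version gives 48, the stated figure. Dropout: 96 / 0.8 = 120. So 77.5 works only as an SD (as a variance it gives n = 1), and the design calculation is between-group.

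**2. SD of the change.** Reading 77.5 as the SD at each visit, SD(change) = 77.5 × √(2(1 − r)):

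- r = 0.7: 77.5 × √0.6 = 60.0 m
- r = 0.8: 77.5 × √0.4 = 49.0 m

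**3. Paired test with no TNHCG effect.** Let both arms rise by m metres. The documents give no value for m, so a range is shown. Take n = 60 per arm, since 3.8 specifies intention to treat with last observation carried forward. The test statistic is noncentral t with 59 degrees of freedom and noncentrality m / (SD/√60); the two-sided .05 critical value is 2.001. For m = 20 and SD = 60.0, the noncentrality is 20 / (60.0/7.746) = 2.58. With p the probability of a significant rise in one arm and the arms independent, significance in the TNHCG arm only has probability p(1 − p).

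| Shared rise (assumed) | Significant rise in TNHCG arm, r 0.7 / 0.8 | TNHCG arm only, r 0.7 / 0.8 |
|---|---|---|
| 0 m | 2.5% / 2.5% | 2.4% / 2.4% |
| 5 m | 9% / 12% | 8% / 10% |
| 10 m | 24.5% / 34.3% | 18.5% / 22.5% |
| 15 m | 48% / 65% | 25% / 23% |
| 20 m | 72% / 88% | 20% / 11% |
| 30 m | 97% / 99.7% | 3% / 0.3% |

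A between-group test on the change favours TNHCG wrongly in 2.5% of trials at every value of m.

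**4. Sensitivity to the SD.** If 77.5 is itself the SD of the change, which also fits 48 per group, the 20 m noncentrality is 20 / (77.5/7.746) = 2.00. The chance of a significant rise is then about 50% with 60 per arm, or 42% with 48.

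**5. Between-group options.** SD relevant to each comparison, with 77.5 as a per-visit SD:

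| Analysis | Formula | r 0.7 | r 0.8 |
|---|---|---|---|
| Week-24 value | 77.5 | 77.5 m | 77.5 m |
| Change score | 77.5√(2(1 − r)) | 60.0 m | 49.0 m |
| Baseline-adjusted (ANCOVA) | 77.5√(1 − r²) | 55.3 m | 46.5 m |

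The variance of ANCOVA relative to the change score is (1 + r)/2, that is 0.85 or 0.90. With 48 per arm, a t test on the change already has 98.9% (r 0.7) to 99.9% (r 0.8) power for 52 m at two-sided .05.

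**The case against.** A reader might infer that a within-group test is the only analysis the plan provides for the primary outcome. The document does not support that. The group t tests in 3.8 apply to all continuous data, a change score is continuous, and both the aim and the sample size are between-group. The paired tests are added to the between-group test and do not replace it. This part of the objection stands in full.

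A reader might also infer that the paired test will often be significant without any effect. That too goes beyond the document. It gives no expected shared change and no proportion of patients entering after an exacerbation, and it also admits stable patients. With no shared change the paired test keeps its nominal level, so the inflation is conditional.

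Nor should the risk be measured by significance in exactly one of the two arms, which is 22–40% at a 20 m rise. Half of those trials are significant in the control arm only, and nobody would report them as a TNHCG benefit.

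Finally, the exact primary model is commonly left to a statistical analysis plan, which is not shown. Its absence alone would be no finding. What does not fall away is what 3.8 positively states: within-group tests under the same significance rule as the between-group test, with nothing to rank the two.

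**Conclusion.** The point holds as a defect of specification. Section 3.8 contains a valid between-group test but does not attach it to the primary endpoint, and beside it stands a test that cannot answer the trial's question, judged by the same threshold.

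The size depends on a shared rise that must be assumed. At 10 m, about a fifth of the 52 m design difference (10/52 = 0.19), a spurious significant improvement in the TNHCG arm appears in a quarter to a third of trials. The more misleading pattern, significant with TNHCG and not with control, reaches at most 25%, against 2.5% for the between-group test. These rates assume 60 per arm, no TNHCG effect and 77.5 as a per-visit SD; the alternative SD reading lowers the 20 m rate for a significant rise to about 50%.

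The plan does not instruct anyone to base the conclusion on the paired test. It leaves that route open. This should be corrected, but it does not undermine the design or the sample size.

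**What to change.** In section 3.8, state that the efficacy conclusion rests on the between-group difference in week-24 6MWD, adjusted for baseline 6MWD by ANCOVA, with its 95% confidence interval and two-sided P-value. With baseline in the model, this gives the same treatment estimate as an analysis of the change, so the endpoint definition can stay. Use the same form for the continuous secondary outcomes.

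Replace the sentence on paired tests with one saying that within-group changes will be reported as means with confidence intervals, for description only and without P-values.

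The cost is two sentences. No patients, visits or data are added, since baseline 6MWD is already needed for the endpoint. Adjustment also lowers the residual SD to about 55–46.5 m, from 60–49 m for the change score or 77.5 m for the week-24 value.

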## Discussion

4

In China, COPD is one of the most commonly occurring respiratory diseases. The latest epidemiological survey shows that the incidence rate of COPD for people over 40 years old is as high as 13.7% with a total of nearly 100 million patients.^[23]^ Although PR in COPD has been widely valued, However, conventional PR exercises require professional equipment, places and personnel, which were not fully applied to the clinic. In China, Tai Chi, Ba Duan Jing, Wu Qin Xi and other traditional Chinese sports are widely used in prevention and rehabilitation of chronic respiratory disease, which has the characteristics of simple movement, suitable strength and no need for special equipment, and is especially suitable for the rehabilitation of COPD. Previous studies have confirmed that it can improve dyspnea, exercise endurance and quality of life, and reduce the frequency of acute exacerbations in COPD patients.^[7,8,24]^ This suggests that traditional Chinese sports are good alternatives to conventional PR for COPD.

TNHCG originated from the Wudang tortoise-shaped posture exercise, which is similar to Tai Chi, and is widely used in Taoist health and rehabilitation centers. Although previous studies^[11–13]^ have shown that Wudang tortoise-shaped posture exercises can improve symptoms, 6-MWT score, and quality of life of patients with COPD, there are some inherent design problems associated with them. For example, the randomization method is not rigorous, blinding and allocation is not described appropriately, correct sample calculation method was not mentioned, and AEs were not recorded in detail. All of these are prone to bias. TNHCG is a set of exercises designed by our hospital specifically for lung rehabilitation of patients with COPD. It targets the pathophysiological areas of COPD such as air trapping and dynamic lung inflation, and contains not only Wudang based tortoise-shaped posture exercises, but also includes lip contraction breathing, abdominal breathing, and acupressure. Although TNHCG has been used in our hospital for nearly 10 years, there has been no relevant research to explore its effectiveness and safety in PR of COPD. Consequently, we designed this randomized controlled trial.

This study may also have some limitations. First, since the aim of the study was mainly to clarify the effectiveness and safety of TNHCG, it has only been compared to a control group that received standard drugs, and not to other conventional PR exercise methods. Therefore, it cannot be concluded whether TNHCG exercise is more or less beneficial than other methods and whether combined use will have a better effect. Second, this is a single-center study with a small sample size. Third, due to limited research funding, we cannot study the mechanism by which TNHCG improves PR. Despite these limitations, we believe that this study will be helpful in elucidating the benefits of TNHCG exercise for PR of COPD. In the future, a multicenter randomized controlled trial with a large sample of patients with COPD must be conducted. Moreover, the mechanism of rehabilitation should be researched.

## Others

5

### Trial status

5.1

This paper is based on protocol version 2.0 dated 29 December 2019. The clinical study began in Jan, 2020, and the approximate date of completion is December, 2021. Currently, participants are being recruited.
